#### Intervention

Figure 3 outlines the four core components of EMPOWER: data analytics, peer support, use of and connection to Whole Health resources, and communication with veterans’ healthcare teams [12, 13]. Data analytics: HUD-VASH case managers identify high-need, HUD-VASH veterans on the Homeless Registry Hot Spot Report. Veterans’ profiles are reviewed to learn about their chronic health conditions, housing status, acute care use, and engagement in supportive care – e.g., primary care, outpatient SUD. Peer support: HUD-VASH peers meet with identified veterans for up to six months, averaging once-per week sessions for the first three months (via phone, video, or in-person), with step-down in frequency as veterans begin to engage in services and reach their goals. By sharing lived experiences, role modeling, and assisting with care navigation, peers build trust, reduce stigma, and motivate patients to engage in services for their health and social needs. This process is structured through a social needs screener – Assessing Circumstances & Offering Resources for Needs (ACORN) [48]. Whole Health: During sessions, peers use a Whole Health approach to collaboratively develop personal health goals that align with the veteran’s priorities and values. Peers help veterans with completing a Personal Health Inventory and developing a Personal Health Plan tailored to their priorities for self- and professional care. Peers help veterans identify action steps to implement their plan, review progress, and problem-solve barriers. Peers also educate the veteran on locally available Whole Health and Complementary and Integrative Health services and provide a warm handoff to a Whole Health Coach, as requested. Provider communications: Peers communicate with a veteran’s care providers to share the veteran’s personal health goals. To this end, peers enter the Personal Health Plan note into the electronic health records (EHR) and include the veteran’s primary care team (if they are enrolled in primary care) and any other providers the veteran identifies as important to their professional care. Peers may communicate with providers to discuss the Personal Health Plan and learn if there are care needs of the veteran for which the peer may be able to help.

**Fig. 3 Fig3:**
[figure not shown]
Core components of EMPOWER

#### Implementation strategies

All sites will receive education and training in the core components of EMPOWER. During the first three months of the project, peers at each site will attend a VA-sponsored, 3-day virtual training in Whole Health. Peers will also be invited to join monthly Whole Health Community of Practice calls hosted by the VA office that supports the implementation of Whole Health VA-wide (Office of Patient Centered Care & Cultural Transformation) and be given access to a SharePoint site housing Whole Health educational materials. Following the Whole Health trainings, EMPOWER virtual trainings will be offered by the first author ([name]). These trainings will cover EMPOWER Manual content, including using Hot Spot reports and completing EHR note templates and Fidelity Monitoring forms.

For the LI strategy of Audit and Feedback, consistent with recommended guidance, data will be provided to participating sites regarding their performance, relative to pre-defined goals, and delivered in multi-modal formats (e.g., visual graphics, written reports) in repeated cycles [49]. Specifically, HUD-VASH peers and supervisors at each site will be emailed monthly automated reports on EMPOWER fidelity data from the EHR (e.g., % of HUD-VASH patients with a Personal Health Plan note) as well as aggregated data on treatment engagement via the Hot Spot dashboard (e.g., % of HUD-VASH veterans with an SUD diagnosis who received SUD specialty care in the past month). The monthly reports will include tailored action item recommendations based on the local site’s performance. Under this LI strategy, sites will not be provided with interactive support to review these reports.

For the HI strategy of Implementation Facilitation, this approach will be tailored to the unique context, goals, and challenges of each site. Consistent with previous implementation work with peers in VA [32], we will employ Implementation Facilitation activities, as described in Table 1. As noted in the implementation research logic model in Fig. 1, the selection of these activities for the current trial was guided by the determinants identified from the literature in terms of implementation of interventions similar to EMPOWER as well as other health-focused interventions in vulnerable populations [38].

**Table 1 Tab1:** Implementation facilitation activities for EMPOWER

Activity	Description
Engagement with the facilitation team	Monthly calls between the external facilitators and site-specific internal facilitators and local champions (if one is identified during pre-implementation)
Audit and feedback	Reports on EMPOWER fidelity data provided monthly to sites’ internal facilitators
Meeting with local opinion leaders	During pre-implementation site visits, meeting with local leaders who are familiar with the site’s organizational procedures and culture, to build consensus and tailor the strategy to the local setting
Problem-solving	Bi-weekly video calls and ad hoc meetings between the Facilitator and peers at a site to troubleshoot challenges such as identifying SMART (Specific, Measurable, Actionable, Realistic, Time-bound) goals with veteran patients
Technical assistance	Assisting HUD-VASH case managers on the use of the Hot Spot reports, and peers on the use of the Personal Health Inventory and ACORN

#### Outcome measurement

The RE-AIM framework [34] will be used evaluate the implementation of EMPOWER. Reach will be measured in terms of the number of patients who are willing to receive EMPOWER, out of all patients that are estimated to be eligible at potential sites. Effectiveness will be operationalized as number of outpatient visits in primary and specialty visits for mental health/SUD care, engagement in Whole Health services offered by sites [50], and premature exits from the HUD-VASH program. Additional patient-level outcomes will include rates of suicide screening and hospitalizations and emergency department visits, particularly for mental health or substance use. All service use variables will be measured in terms of receipt in VA and in the community using data from CDW. Adoption will be measured in terms of the number of peers in HUD-VASH at sites that are trained in EMPOWER and initiate the intervention with eligible patients at their site. Implementation will be operationalized in terms of fidelity to the various elements of EMPOWER at the site level, as measured via activity logs embedded in the EHR and electronic data capture logs (e.g., Qualtrics) to document type and length of encounters. Maintenance will be measured by the number of patients who are continuing to engage in EMPOWER and other VA services over the duration of the intervention (i.e., 6 months). To supplement the quantitative data used to operationalize the RE-AIM domains, we will conduct semi-structured qualitative interviews by phone with six key informants at each site – e.g., HUD-VASH peers, supervisors, and case managers (n = 36). The interview questions and format will be aligned with the qualitative data collection methods described above in Aim 1.

#### Analysis

We hypothesize the HI (vs. LI) implementation strategy will have a greater impact on the RE-AIM outcomes*.*For each outcome, we will specify Generalized Linear Mixed Effects models (GLMMs) using unstructured correlation matrices for random effects to flexibly account for variation over time within patients and variation over time within cluster sites with patients clustered within sites [51]. Individual patients may be observed in both LI and HI (thus unbalanced within clusters over time, with some observed multiple times and others at only one stage of implementation). Random effects components of the GLMM will account for this unbalanced panel nature of patient eligibility and site volume in any given time point [51]. In addition to the staircase design’s randomization providing some protection from confounding influences, we will include both patient- and site-level covariates to improve efficiency of the treatment estimates. At the patient level, we will account for demographics to explore potential variations in effectiveness based on these factors (interaction terms). At the site level, we will account for covariates that may represent confounders despite randomization, including site patient volume normalized by providers at the site (site capacity and time to meet patient needs) and staffing changes. Communication with the sites will enable us to identify other factors affecting implementation that we may want to account for in models that may affect the relative success of HI over LI, or vice versa.

Because Reach can be assessed as counts or rates of patients, we will specify Poisson GLMMs. For predicting individual reach to a veteran (a binary outcome), Poisson GLMMs with robust standard errors will be fit to allow convergence and provide accurate treatment estimates [52]. Because EMPOWER will afford more opportunity time in HI than LI to achieve outcomes, the Poisson GLMM approach allows a facile offset term to account for the different opportunity lengths for LI and HI conditions. At the patient level, time dynamics can be nuanced because care-seeking is dynamic and may represent residual confounding for which site-level randomization cannot account. Specifically, patients who seek more care may have a greater dosage of exposure to the condition the site is in at a particular time. Accordingly, we will also account for the longitudinal number of encounters (via stop codes) a patient has in the site and offset those encounter opportunities in the Poisson GLMM. This effort is aimed at improving precision of estimates of LI and HI effects in the models.

### Aim 3

To examine the implementation costs of EMPOWER, we will use a sequential mixed-methods design where an initial qualitative phase informs customization of the typical quantitative approach of a budget impact analysis [53]. Consistent with Eisman and colleagues’ work [54], we will conduct semi-structured interviews to identify stakeholder perspectives, which will guide the level of detail to be employed in micro-costing – e.g., including different payers’ relative priorities on how they may use cost information for implementation planning. We will use rapid qualitative methods, as described above in the Methods section for Aim 1. Interview participants will be drawn from a Learning Community of regional and national VA stakeholders associated with project and other medical center leadership.

Quantitative data collection and a budget impact analysis (BIA) will then proceed, informed by the needs of operational partners and clinical leadership. Budget impact analyses are conducted from the perspective of the entity that pays for the intervention (“payer”). Because implementation of EMPOWER requires resource allocation across different contexts, we will adopt three payer perspectives, all of which will be represented in the qualitative phase: (1) HUD-VASH – the relevant national program office, (2) Veteran Integrated Service Networks, and (3) VA facilities. Consistent with best-practices for conducting a BIA [53], we will include costs necessary to deliver EMPOWER (e.g., peer time to conduct veteran meetings), as well as ensure it is appropriately delivered in practice (e.g., Whole Health trainings). Costs incurred only for the evaluation of the implementation (e.g., time collecting payer perspectives) and fixed costs that later sites would not incur (e.g., development of reporting tools) will be excluded.

Costs of specific elements of EMPOWER (e.g., staff time) that have existing values will be obtained using the VA’s Managerial Cost Accounting Office’s data in CDW [55]. Because implementation strategies do not have a standard value, we will estimate their cost using activity-based costing from time use data gathered using an electronic data capture system [56]. Activity-based costing emphasizes the role of staff effort devoted to different activities within a strategy. Where indicated by the Learning Community, additional elements of strategy costs may be micro-costed as well. The BIA will report (1) expected implementation cost for implementation of EMPOWER at future sites, (2) comparative implementation cost for the LI and HI strategies, and (3) expected sustainment cost over a relevant budget period. Indexing time, from the beginning of implementation of EMPOWER, all costs will be assigned to a stage of implementation (pre-, during-, post-) using standard methodology [57]. Based on Learning Community feedback, we will consider additional perspectives and cost analysis methods to our approach (e.g., implementation cost-effectiveness analysis, analysis of variation in costs by effort level of involved personnel).

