**Methods:**

(Aim 1) At 7 sites in the Veterans Health Administration (VA), a mixed methods pre-implementation evaluation will identify determinants and their potential impact on uptake of EMPOWER and inform modifications to the intervention and implementation strategies as needed. (Aim 2) A staircase cluster randomized design will evaluate the rollout of the implementation strategies, beginning with Audit and Feedback (low-intensity) and then switching to Implementation Facilitation (high-intensity) after 6 months. Implementation Facilitation is hypothesized to have a greater impact on the reach, effectiveness, adoption, implementation (fidelity), and maintenance of EMPOWER. (Aim 3) A budget impact analysis will estimate the average cost of implementing EMPOWER at future sites and comparative costs for implementing the low- and high-intensity strategies.

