#### Design

We will conduct an adaptation of the multi-site hybrid type 3 cluster randomized staircase stepped-wedge trial, evaluating the implementation of EMPOWER while gathering data on its effectiveness. The staircase design is an adaptation to stepped wedge designs (SWD) that accommodate more flexible implementation (i.e., less burden to sites and clinicians). At the same time, it offers robust statistical efficiency given that statistical information is often strongest around time periods in the SWD when switching from one implementation strategy to another [44]. For EMPOWER, of interest is the effect of switching from Low Intensity (LI) to High Intensity (HI) implementation strategies. An imbalanced design [45] will be employed in which sites will spend twice as long in HI than LI (see Fig. 2). The use of an imbalanced design further accommodates the anticipated needs of sites to be enrolled in EMPOWER.

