#### Sample

At each implementation site, eligible patients will be identified from VA’s Homeless Registry “Hot Spot” reports, which use real-time data on acute care service utilization to identify high-need, housing-insecure patients [7, 46]. These reports identify veterans on the VA Homeless Registry (i.e., those who had received VA housing services in the past two years) who had ≥ 1 hospital admissions and/or ≥ 2 ED visits in the past quarter of the fiscal year [47]. Reports are housed on VA’s Support Services Center (VSSC) website with data primarily drawn from the Corporate Data Warehouse (CDW). Data for the reports are updated nightly and separate reports are generated for those who are (and are not) enrolled in VA primary care. From these reports, we will identify patients at each implementation site who are (a) currently enrolled in HUD-VASH, (b) have a mental health and/or SUD diagnosis, and (c) have not been engaged in either primary care or mental health during the quarter that they were flagged on the report. Approximately 585 patients across the target sites are estimated to be eligible to receive EMPOWER during the project period.

Power was assessed by testing a total of 448,560 plausible scenarios for a binomial outcome (e.g., patient reach) with the effect size (θ) of central interest being the mean difference in proportion of patients reached when moving from LI to HI. We assessed the necessary number of patients to achieve Power = 0.80 at α = 0.05, by including a random intercept for each cluster in the analyses (τ) is ∈ {0.01, 0.05, 0.10, 0.15} with θ ranging from 0.01 to 0.20 increase in number of patients reached and an autoregressive correlation of 0.7 between LI and HI implementation periods. Under a variety of plausible scenarios, we assessed power in relation to sample sizes ranging from a total N of 200–1000 patients (the plausible lower and upper limits, respectively, of patients eligible for EMPOWER). We observed Power = 0.80 to be achieved in sample size ranges between 227 and 278 patients.

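### Without a fixed calendar-time term, the Aim 2 models would count most of a linear trend shared by the sites as an effect of the high-intensity strategy

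*Protocol article*

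**What the plan says.** The Abstract (Methods) gives one order for all seven sites: "beginning with Audit and Feedback (low-intensity) and then switching to Implementation Facilitation (high-intensity) after 6 months". The Aim 2 Design section adds that "sites will spend twice as long in HI than LI", which implies about 12 months of HI after 6 of LI.

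The Aim 2 Analysis section specifies a generalised linear mixed model for each outcome, "using unstructured correlation matrices for random effects to flexibly account for variation over time within patients and variation over time within cluster sites". The named covariates are patient demographics, site volume per provider and staffing changes. For Reach, the section adds Poisson models with offsets for the unequal length of LI and HI and for the number of patient encounters. On bias, it refers to "randomization providing some protection from confounding influences, we will include both patient- and site-level covariates to improve efficiency of the treatment estimates". It then allows that some site-level covariates may be confounders in spite of randomisation. It names no fixed effect for calendar period or for time since a site's launch.

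The power description in the Sample section names a random intercept per cluster and a correlation of 0.7 between the LI and HI periods. It mentions no period effect.

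**The concern.** In a staircase design, randomisation decides when a site starts. It does not decide the order of conditions, because HI always follows LI. Staggered starts help because at one calendar time some sites are in LI and others in HI, but an analysis uses that comparison properly only if calendar time is in the mean model.

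The listed components do not do this job. Site and patient random effects have mean zero, so they describe departures from a common mean and are a poor substitute for a change in that mean. Offsets correct for length of exposure, not for a rate that changes over time. Volume per provider and staffing changes may track part of a trend, but only by chance.

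At stake is the reading of a positive result. If reach or care engagement was rising at all sites for unrelated reasons, part of that rise would be reported as benefit of facilitation, and the budget comparison of the two strategies would be read alongside it.

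**Working it through.** **The plan's own figure.** The Sample section reports "Power = 0.80 at α = 0.05" reached with 227 to 278 patients. This can be neither confirmed nor refuted: baseline reach, sidedness and the combination of effect size and cluster variation behind the range are not given. Simple two-proportion calculations give totals from about 100 to about 880. Some fall inside the range: for a difference of 0.15, two-sided, a baseline of 0.1 with 1:2 allocation gives 234, and a baseline of 0.2 with 1:1 gives 276.

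**Inputs.** From the article: 7 sites, 6 months of LI, HI twice as long (12 months), about 585 eligible patients, and "θ ranging from 0.01 to 0.20 increase in number of patients reached". Assumed: even patient flow over months, 25% baseline reach, τ read as a standard deviation of 0.05 on the proportion scale, and starts staggered by 3 or 6 months.

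**Step 1, distance between phases.** LI midpoint = 6/2 = 3 months. HI midpoint = 6 + 12/2 = 12 months. Distance = 9 months.

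**Step 2, bias with a site random intercept.** Every site has the same one-third to two-thirds split, so comparing sites carries no information on HI. The estimate is the average within-site difference, HI mean minus LI mean. Under a shared linear trend of slope b per month its expectation is (true effect) + 9b, whatever the stagger or τ. A generalised least squares calculation gives 9.0 months for staggers of 0, 3 and 6 months.

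- 10 points per year: 0.10 × 9/12 = 0.075.
- 5 points per year: 0.05 × 9/12 = 0.0375.
- On the rate scale, drifts of 1%, 2% and 3% per month give about 1.01^9 = 1.09, 1.02^9 = 1.20 and 1.03^9 = 1.30. A Poisson simulation with no HI effect gave 1.09–1.10, 1.21 and 1.31–1.33.

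**Step 3, richer random effects.** A random site slope absorbs part of the trend, because a large slope variance approaches a separate fixed slope per site. With a slope SD of 0.005 per month, about 8.2 of the 9 months remain. With a very large SD (0.02 per month), about 3.5 remain. Site-by-time autoregressive effects leave 8.7 to 8.8, and a random period effect shared by sites leaves 7.5 to 9.0.

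**Step 4, adding a fixed calendar term.** With staggered starts, a linear term or quarter indicators reduce the carry-over of a linear calendar trend to 0. If all sites started together, quarter indicators could not be separated from HI.

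**Step 5, precision.** Without a time term, 585/3 = 195 patients are in LI and 390 in HI, so SE = √[0.25 × 0.75 × (1/195 + 1/390)] = 0.038. With a time term it is 0.042 (linear, 6-month stagger) to 0.051 (quarter indicators, 3-month stagger). The ratios are 0.042/0.038 = 1.11 and 0.051/0.038 = 1.34; squared, about 1.22 and 1.80. Rough scaling of the stated range gives 227 × 1.22 ≈ 277 to 278 × 1.80 ≈ 500. With 30% baseline reach, τ of 0.15, a 3-month stagger and quarter indicators, the SE goes from 0.0402 to 0.0665, a variance ratio of about 2.7, which gives about 620 to 760.

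**Step 6, maturation since launch.** A calendar term does not remove this. Across the structures tried, about 3 to 8 of the 9 months of a linear maturation effect still load on HI. If sites improve steadily over 6 months and then level off, the LI average is half the rise and the HI average is the whole of it, so without a time term 0.5 of the rise loads on HI. With calendar terms it is still about 0.4 to 0.5.

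**The case against.** The strongest reply is that silence is not exclusion. The article does not write out the fixed part of the model, its site-level covariate list is open, and it says further factors may be added after talking with sites. Fig. 2, captioned as the analytic approach, is not visible here and could show a period term, and a separate analysis plan could contain one. This stands as a limit on certainty. It does not remove the point, because the text takes up time explicitly and assigns it to random effects and offsets. An analyst who followed it as written would fit no common time term.

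Four stronger readings are tempting and are not supported.

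- A reader might infer that any shared trend goes wholly to HI. That is exact only for a linear trend with a random intercept. The article plans more flexible random effects, which remove part of it.
- A reader might infer that maturation is completely inseparable from condition. Months since launch vary within LI and within HI, so a linear slope can be separated from a step at the switch. What cannot be separated without assuming a shape is a general learning curve.
- A reader might quote a high false-positive rate. Any such rate depends on a trend that the article does not quantify. Robust tests with seven clusters also over-reject on their own: a Poisson GEE check with neither trend nor effect rejected in 14% of 300 runs.
- A reader might say that the target contrast is misdescribed. The Design section already defines it as the effect of switching from LI to HI.

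**Conclusion.** The point holds for the model as described. With no fixed calendar-time term, and LI always before HI, most of a linear trend shared by the sites stays in the HI coefficient: all 9 months with a site random intercept, about 8 with modest random slopes, and less if slopes vary greatly. At an assumed 10 points per year that is up to about 7.5 points, over a third of the largest planned effect (0.075/0.20 = 38%). The article does not show that such a trend exists, so this is an exposure to bias and not a demonstrated bias.

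The 9-month figure rests on the derived 12 months of HI and even patient flow. It does not depend on the stagger, baseline reach or τ. The precision figures do depend on those assumptions. Maturation since launch is a separate problem, which a calendar term leaves largely in place.

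**What to change.** 1. In the primary models for Reach and the patient-level outcomes, name a parsimonious fixed calendar-time term: linear, a low-order spline, or quarter indicators where the data support them. Adoption and site-level fidelity, with seven sites, may not support quarter indicators.
2. Pre-specify a sensitivity analysis with a slope in months since launch plus a step at the switch, and state that it separates maturation from HI only under that shape.
3. Name a small-sample method for inference with seven sites.
4. Recheck the 227 to 278 patients with the time term included, giving baseline reach, sidedness, effect size and stagger.
5. If Fig. 2 or a separate plan already contains a period term, say so in the Analysis text.

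The cost is mainly precision. The standard error rises by about 10 to 35% with 25% baseline reach, τ of 0.05 and a 3- to 6-month stagger, and by more under other structures. The rough scaling puts the requirement at about 277 to 500 patients in the first case and about 620 to 760 in the least favourable case, against about 585 eligible, so the margin for 0.80 power may shrink or disappear.

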### Objectives and aims

In this paper, we describe the protocol for a multi-site trial to evaluate the implementation of EMPOWER with high-need, HEVs in the Housing and Urban Development (HUD) and VA Supportive Housing (VASH) program. HUD-VASH is the largest permanent supportive housing program in the US, housing over 180,000 veterans since fiscal year 2012. HUD-VASH has two goals: (a) assist HEVs with obtaining permanent supportive housing, and (b) facilitate access to healthcare and psychosocial services for veterans to maintain housing [33]. The overarching objectives of the current trial are to implement and evaluate EMPOWER at 7 VA sites by (Aim 1) identifying pre-implementation barriers and facilitators to make fidelity-consistent modifications to the intervention and to refine implementation strategies for the local settings; (Aim 2) using a hybrid type 3 staircase cluster randomized trial to test the implementation of EMPOWER through tailored low-intensity (Audit and Feedback) and high-intensity strategies (Implementation Facilitation); and (Aim 3) conducting a multi-payer economic analysis. Implementation outcomes will be evaluated using the Reach, Effectiveness, Adoption, Implementation, and Maintenance (RE-AIM) framework [34]. We hypothesize that the high-intensity implementation strategy of Implementation Facilitation will have a greater impact on all RE-AIM outcomes than the lower-intensity strategy of Audit and Feedback.

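### With 7 randomised sites, uncorrected robust standard errors for binary reach can inflate type I error, and the unstructured site-level random-effects matrix is rarely estimable

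*Protocol article*

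**What the plan says.** The objectives state that the trial will "implement and evaluate EMPOWER at 7 VA sites". Under Aim 2, Design, the site is the unit that moves from the low-intensity (LI) to the high-intensity (HI) strategy.

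Under Aim 2, Analysis, each outcome gets a generalised linear mixed model (GLMM) "using unstructured correlation matrices for random effects", to capture change over time within patients and within sites. For reach, Poisson GLMMs are planned. For the binary patient-level version, "Poisson GLMMs with robust standard errors will be fit to allow convergence and provide accurate treatment estimates". Robust standard errors are named nowhere else.

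The section does not say whether the robust variance is clustered by site or by patient, whether a normal or t reference is used, or whether a few-cluster correction applies. It gives no fallback for the random-effects structure. The power work under Sample used a random intercept per cluster, which is simpler than the analysis model, and reports no check of type I error.

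**The concern.** A robust variance clustered by site is built from 7 independent contributions. With so few, the uncorrected estimate is on average too small and also unstable, and a normal reference allows for neither. Tests of HI against LI on reach could then be significant too often. Reach is the plan's own example outcome for power, and HI against LI is its main hypothesis, so a false positive would favour the more intensive strategy.

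The unstructured matrix is a different matter. With q site-level random effects it has q(q+1)/2 parameters: 3 for an intercept plus an HI slope, and 6 for three periods. Seven sites carry little information on these. The likely outcome is a variance of zero, a correlation of ±1 or a failed fit, after which the analyst must choose a simpler model with the data in view. Robust standard errors do not help here, because they are computed after the model has been fitted.

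**Working it through.** **The plan's own figure.** The document states no realised type I error. Its one related figure is power: "We assessed the necessary number of patients to achieve Power = 0.80 at α = 0.05", with the answer 227 to 278 patients. This cannot be reproduced, because the baseline proportion is not given and the effect is a range ("θ ranging from 0.01 to 0.20 increase in number of patients reached"). Simple two-proportion formulas fall in or near 227–278 for many combinations with a difference of about 0.15–0.18, but need about 1,400 to 3,500 patients at 0.05. The figure says nothing about type I error with 7 sites.

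**Inputs from the protocol.**
- Nominal α of 0.05 (two-sided assumed).
- 7 sites.
- About 585 eligible patients, so 585/7 ≈ 84 per site.
- LI for 6 months, then HI for twice as long.
- Correlation of 0.7 between LI and HI periods.
- "random intercept for each cluster in the analyses (τ) is ∈ {0.01, 0.05, 0.10, 0.15", whose scale is not stated.

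**Closed-form check.** If the site-level test statistic behaves like t on 7 − 1 = 6 degrees of freedom but is compared with 1.96:
- 2·P(t₆ > 1.96) = 9.8%.
- With 5 degrees of freedom, 2·P(t₅ > 1.96) = 10.7%.
- If the uncorrected variance is also too small by a factor 6/7, the effective cut-off is 1.96 × √(6/7) = 1.81, and 2·P(t₆ > 1.81) = 12.0%.

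**Simulation under no effect.** There were 2,000 runs in each of 10 scenarios (Monte Carlo standard error at 15%: √(0.15 × 0.85/2000) = 0.8 points). Each run had 7 sites with one LI and two HI six-month periods. Across scenarios these settings varied: 3 or 7 staggered sequences; N of 585 or 250; reach of 0.4 or 0.2; site-period SD from 0.01 to 0.155; autocorrelation of 0.7 or 1; and time adjustment by none, linear trend or period effects. The sequence layout, the baseline reach and the scale of τ are assumptions.

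| Standard error and reference | Type I error, range over scenarios |
|---|---|
| Site-level robust, uncorrected, normal: unstructured GLMM | 13.6–17.5% |
| As above: random-intercept GLMM | 12.2–17.2% |
| As above: marginal Poisson (GEE) | 12.4–17.0% |
| Site-level robust, uncorrected, t on 6 df | 6.5–10.0% |
| Patient-level robust, site fixed effects, normal | 5.1–14.0% |
| Model-based, normal: random-intercept GLMM | 1.1–8.2% |
| Model-based, normal: unstructured GLMM | 1.1–7.6% |
| GEE, Mancl-DeRouen correction, normal | 5.4–8.0% |
| GEE, Mancl-DeRouen correction, t on 6 df | 2.1–3.8% |

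The patient-level rate depends on the site-by-period variation. With N = 585, reach 0.4, autocorrelation 0.7 and a linear trend, it was 5.8% at SD 0.05, 9.5% at 0.10 and 14.0% at 0.155. At SD 0.10 without time adjustment it was 11.7%.

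**Estimability.** For an unstructured site intercept plus HI slope, the share of fits with an interior solution ran from 0.05% to 25.15%. So 74.85% to 99.95% of fits ended on the boundary.

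Patient-level random effects, covariates and repeated observation of patients were not simulated.

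**The case against.** The strongest reply is that this is a condensed article. Clustering level, reference distribution and small-sample correction are details that an analysis plan commonly holds, and nothing in the article rules a correction out. The robust errors can also be read as a repair for fitting a Poisson model to a binary outcome, with site clustering left to the random effects. This stands in part, and it rules out four stronger readings that a reader might reach:

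- **The plan necessarily at least doubles the false-positive rate.** That needs three unstated choices together: site-level clustering, no correction and a normal reference. Other readings gave 1% to 14%.
- **Every RE-AIM contrast is affected.** Robust errors are named only for binary reach, and the other outcomes were not simulated.
- **Clustering by patient would be worse.** Its range (5.1–14.0%) lies mostly below the site-level range (12.2–17.5%).
- **The unstructured matrix drives the inflation.** With model-based errors it performed like the random intercept (1.1–7.6% against 1.1–8.2%). Nor does any text propose monthly random effects, so very large parameter counts have no basis.

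The reply does not dispose of the point. The unstructured matrix and the robust errors are stated choices, presented as sound, and they perform poorly or are rarely estimable with 7 sites. A separate analysis plan that dropped the unstructured matrix would contradict this article.

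**Conclusion.** The concern holds in limited form. For binary reach, site-level robust errors without correction and with a normal reference give about 12–17% type I error at nominal 5%. With patient-level clustering it is about 5–14%, depending on site-by-period variation and time adjustment. Separately, for each outcome, the unstructured site-level matrix is rarely estimable from 7 sites, with boundary fits in about 75% or more of simulations even in its smallest form. That is an estimability fault which leaves room for post hoc simplification, and not a source of false positives.

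The sizes rest on an assumed staircase layout (Fig. 2 was not available), an assumed baseline reach and an assumed scale for τ. The direction is stable, since uncorrected site-level errors exceeded 12% in all 10 scenarios. The number of sites also needs reconciling: the interviews are described as "six key informants at each site – e.g., HUD-VASH peers, supervisors, and case managers (n = 36", and 36/6 = 6 sites, which would leave fewer degrees of freedom than 7.

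**What to change.** 1. Replace the unstructured site-level matrix with a prespecified random site intercept plus random site-by-period effect. State the fallback in advance, for example dropping the site-by-period term if its variance is estimated at zero.
2. For binary reach, state that the robust variance is clustered by site, uses a small-sample bias correction (Mancl-DeRouen or Kauermann-Carroll) and is referred to t with degrees of freedom based on the number of sites (6 for 7 sites). Changing only the reference to t is not enough, since the uncorrected error stayed at 6.5–10.0%.
3. Add a site-period summary analysis with site and period effects as a sensitivity check. In a further null simulation, such an analysis with t on 5 df rejected in 4.7%. The 5 df assume one site per sequence and must be set from the actual layout. It should not replace the main model, because it would give up the planned patient-level covariates and encounter offset.

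Cost: no change to conduct or data collection. Intervals widen (the 5% critical value on 6 df is about 2.45 against 1.96). The test becomes somewhat conservative: Mancl-DeRouen with t on 6 df rejected in about 2–4%, tested on the marginal Poisson model only. Kauermann-Carroll was not simulated. Because power will fall, the power statement should be rerun under the chosen method.
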